## Abstract

**Introduction: **Resistance exercises and dietary protein have been shown to reverse frailty, yet they are not commonly offered in clinical practice. We aim to measure changes in health outcomes, including physical frailty status (SHARE-FI), clinical frailty status (CFS) and muscle mass, as a result of an optimised exercise and dietary intervention versus usual care in a primary care (PC) setting. The intervention has been derived from our systematic review and meta-analysis findings and optimised through patient and public involvement and multidisciplinary team input.

**Methods: **This study is a multicentre randomised controlled parallel arm trial with a three month follow up. 210 eligible people aged 65 and over, no more than mildly frail, will be recruited in seven PC practices in Ireland and randomly assigned to ‘intervention’ or ‘usual care’. Intervention participants will be provided a leaflet with strength exercises, protein dietary guidance and educational discussion. Baseline measurements will include demographics, health indicators, comorbidities, malnutrition universal screening tool (MUST), frailty status (SHARE-FI, CFS) and muscle mass (bioelectrical impedance). Primary outcome will be frailty status measured by SHARE-FI at three months. Secondary outcomes include CFS, muscle mass, in-patient hospitalisation, long term care admission, and subjective ease of intervention and difference to general health. Statistical analysis will be undertaken by an independent statistician.

**Discussion: **The diversity of tested frailty interventions and lack of clear guidance may contribute to low implementation rates. The REFEREE trial focusses on an optimised intervention for a syndrome that poses growing individual and societal challenges. It is hoped results can encourage mainstream adoption of interventions to reverse clinical frailty and build resilience in primary care.

**Trial registration: **ClinicalTrials.gov ID
NCT04628754; registered on 13 November 2020.

## Introduction

### Background information

Frailty can be conceptually described as a state of physiological vulnerability to external stressors. It increases the risks of illness, falls, dependency, disability, and death
^1,
2^. Frailty has been described as the most problematic expression of population ageing
^2^.

The challenge of frailty is heightened by our aging population and increased life expectancy. The UN estimates that the population of over 60-year olds will more than double from 2017 to 2050
^3^. In Ireland, the population of over 65-year-old is growing four times faster than the total population. The prevalence of frailty is estimated at 11% in adults aged ≥50 years and increases to some 50% in those >80 years of age
^4,
5^.

General Practitioners (GPs) are in a unique position to engage with and support their aging patients. Since 2017 the new General Medical Services (GMS) contract in England mandates that all primary care practices use an appropriate tool to identify patients aged ≥65 years who are living with moderate or severe frailty. GPs are also obliged to offer appropriate interventions. Such a mandate to screen and intervene to address frailty is fast becoming international best practice. However, there has been little guidance on the best interventions until recently.

We conducted a systematic review of frailty interventions in primary care, reviewing 925 studies and analysing 46 in detail
^6^. We found that frailty can be delayed and reversed. Results have been further refined and strengthened in our meta-analysis
^7^.

Interventions with both muscle strength training and protein supplementation were consistently placed highest for effectiveness and ease of implementation.

### Rationale for the study

Resistance training done at home and protein supplementation have been shown to be the most effective and easiest to implement interventions to reverse frailty and build resilience. However, it is not common practice to offer and support such interventions in primary care.

Frailty is related to day-to-day symptoms, co-morbidities, disabilities, and overall physical and cognitive functioning. A composite measure of all the latter, guided by the clinician’s clinical judgement, can be assessed by the Clinical Frailty Scale (CFS)
^8^. The use of the CFS has become quite widespread in clinical practice in many countries.

On the other hand, physical frailty status is a narrower concept based on unexplained weight loss, self-reported exhaustion, weakness (by grip strength), slowness (by gait speed) and low levels of self-reported physical activity
^9^. Researchers have adapted the physical frailty definition to allow the provision of a continuous score (e.g. SHARE-FI
^10^). A core component of the physical frailty phenotype is the diagnosis of sarcopenia, which has been operationalised by consensus
^11^ and objectively measured with bioelectrical impedance analysis. Bioelectrical impedance analysis is a safe, non-invasive, rapid and relatively accurate way to assess body composition. Limitations include reduced accuracy for people with BMI > 34 kg/m
^2^, though the technology remains acceptable for monitoring changes in body composition over time.
Figure 1 shows the conceptual framework of the different frailty operationalisations used in this study.

**Figure 1. f1:**
[figure not shown]
Conceptual framework of the different frailty operationalisations used in this study.

Recruitment based CFS seems the most inclusive, but baseline measures will be obtained of all measures at baseline and follow up.

This study provides an opportunity to share an optimised intervention with community-dwelling adults aged 65 and over, whose baseline CFS is not worse than mild (i.e. 5 or less), evaluate improvements in health outcomes and demonstrate how the intervention may be incorporated efficiently in clinical practice. The results are intended to encourage mainstream adoption of practical interventions to reverse clinical frailty and build resilience in primary care.

An intervention with ten recommended resistance exercises and dietary guidance on protein consumption has been derived from findings of our systematic review
^6^ and meta-analysis
^7^ and optimised through a patient and public involvement (PPI) process.

### Feasibility study

Feasibility of the exercise component of the intervention was assessed in a study in 2019 and 2020
^12^. The findings have been key to refining the intervention for this RCT. We offered an exercise intervention to reverse frailty and build resilience in primary care consultations. We set out to assess uptake of the exercise regime; ratings of its ease and subjective health after participation; how a follow-up telephone-call might affect compliance and overall feasibility. We applied the Bowen feasibility model
^13^ which has been successfully used in assessing public health and preventive medicine interventions. This feasibility model tests eight areas of focus: acceptability; demand; implementation; practicality; adaptation; integration; expansion; and limited-efficacy testing. Selected results include:

A total of 94 of 107 eligible people (88%) participated (average age 77, 59 females (63%)). 95% of females and 78% of males enrolled. Only 15% had previously considered resistance exercises.

Participants found the exercises both easy to follow and generally easy to do. Overall, 32% described exercises as ‘very easy’, 55% ‘somewhat easy’, 7% ‘neither easy nor hard’, 6% ‘somewhat hard and 0% ‘very hard’.

At one month, 66% of participants called were exercising regularly (76% of females, 50% of males). At two months, compliance among those who had not been called at one month was: 65% (67% of females, 62% of males). However, compliance among those previously called was higher: 78% (88% of females, 63% of males). 64% of those who were not doing exercises at one month had taken them up following the single phone call (67% of females, 63% of males).

Many described how the home-based exercises helped with staying active and reducing anxiety while housebound during the Covid-19 pandemic

The majority of participants self-reported their general health had improved as a result of doing the exercises and none reported feeling worse. 14% felt ‘much better’, 52% ‘slightly better’, 34% ‘about the same’, 0% ‘slightly worse’, and 0% ‘much worse’

Each of the eight areas of focus of the Bowen feasibility model have been addressed and satisfy overall feasibility. Publication of this feasibility study is pending.

### Public and patient involvement

Public and patient involvement in health involves undertaking research with members of the public rather than for them. As PPI has been a key consideration within Irish health research culture, we wanted to enable the involvement of potential participants’ in co-designing our RCT to ensure that their priorities were at its core. We built on two group discussions with 24 over 65-year olds, when introducing an exercise regime in a previous service evaluation study
^14^, and 145 one-on-one discussions listening to feedback during the feasibility study. We wished to learn additionally from participants in three online workshops to optimise our patient communication model, refine the exercise regime and develop dietary guidance for a future trial.

We convened three online group workshops with older adults involved in the feasibility study. The group size of an average of 5 participants and 2 researchers was in keeping with best practice for conducting both group-based action learning
^15^ and focus group activity
^15,
16^. Key themes and questions for each workshop were prepared in advance. A Socratic approach of open questions with active listening was used in order to ensure the voices of the non-researchers are primarily heard. Transcripts were analysed and key feedback synthesised under the headings of: ‘patient engagement and communication model’, ‘exercise regime’ and ‘dietary guidance’. Analysis used both an inductive and deductive approach drawing on normalisation process theory. Our approach was guided by a framework for effective and meaningful public and patient representative (PPR) involvement in health research
^17–
19^, which includes operating in a structured environment; managing expectations and ensuring roles are clear; providing support for successful participation and ensuring inclusive representation; and commitment to co-learning involving institutional leadership.

PPI output included strong endorsement from participants for offering this intervention; co-design of the patient communication model; inclusion of preferred setting, medium and gender balance for the exercise regime; and co-design of the dietary guidance content.

### Benefits and risks

The systematic review
^6^ identified benefits to patients that include decreased risks of illnesses, falls, dependency, disability and improved mortality. 71% of studies measuring impact on frailty status demonstrated significant improvement. 69% of studies measuring impact on singular frailty indicators or other criteria demonstrated significant improvement. The exercises create a small risk of musculoskeletal strain. No such adverse event was recorded during a feasibility study of the intervention, prior to PPI optimisation. The risk was mitigated by the fact that the exercises are simple in nature and the supporting patient information leaflet advises thirty second breaks between exercises and not to undertake any exercise that causes pain. Risk is further mitigated by excluding participants with CFS 6 and above. The risk (probability) of harm is considered to be low.

## Study objective

### Primary objective

To measure changes in health outcomes, including physical frailty status (SHARE-FI), clinical frailty status (CFS), muscle-mass, as a result of an optimised exercise and dietary intervention versus usual care among community-dwelling adults aged 65 and over whose baseline clinical frailty (CFS) is not worse than mild.

### Secondary objective

To understand participants’ perspectives on the ease of the intervention and personal health benefits.

### Primary and secondary endpoints/outcome measures

***Primary outcomes***

 Frailty status measured by SHARE-FI at three months after the start of intervention.

***Secondary outcomes***

 Clinical frailty status measured by CFS at three months after the start of intervention. Muscle mass measured by bioelectrical impedance at three months after the start of intervention.Body fat, bone weight, base metabolic rate, biological age by bioelectrical impedance at three months after the start of intervention. Incidence of in-patient hospitalisation during follow-up. Incidence of long-term care admission (LTC) during follow-up. Ease of the intervention measured on a five-point scale: ‘very easy’, ‘somewhat easy’, ‘neither easy nor hard’, ‘somewhat hard’, or ‘very hard’ three months after the start of intervention. Difference to general health as a result of the exercises measured on a five-point scale: ‘much better’, ‘slightly better’, ‘about the same’, ‘slightly worse’ or ‘much worse’ three months after the start of intervention.

## Trial design

### General considerations

This multi-centre, randomised controlled, parallel arm trial aims to measure the effectiveness of an optimised primary care intervention to reverse frailty and build resilience versus usual care, among pre-frail and mildly frail adults aged 65 and over. The trial will take place in Ireland. Enrolment will take place in seven GP practices in Dublin and Wicklow over a period of six months. All measures will be collected in the GP practice setting. A clear training plan and documentation will be provided to GPs at each site to mitigate the risk of recorded and unrecorded protocol deviations
^20^. A study scheme is shown in
Figure 2.

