Intervention participants will be called after one month and after three months by the GP and asked if they had followed the exercise regime (and for how long and how many times a week) and dietary guidance. At three months they will be asked if they found the exercises ‘very easy’, ‘somewhat easy’, ‘neither easy nor hard’, ‘somewhat hard’, or ‘very hard’; and had they noticed any subjective difference to their health as a result of the intervention, namely feeling ‘much better’, ‘slightly better’, ‘about the same’, ‘slightly worse’ or ‘much worse’. All participants will be invited to return at three months for a clinical assessment and measurement of health indicators and frailty status as described above by the GP. Participants will be invited to return for subsequent one year follow up appointments. This 12-month follow up will be subject to a further ethics committee review. The follow up visits will be free of charge. A schedule of events for baseline, one-month call and three months follow up are shown in
Figure 3.

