### Determination of sample size subjects

We have calculated a sample size of 176 with the following parameters: Two independent study groups (i.e., control and intervention); outcome measure of frailty status (i.e., change from frail or pre-frail to non-frail as measured by SHARE-FI); improvement of frailty status in the intervention group to non-frail of 15%, allowing for a 3% improvement in the control group due to bias; enrolment ratio of 1; probability of type I error of 5% (0.05); power 80%. Enrolment of 210 participants assumes a 15% drop out rate.

Sample sizes in comparable trials include Binder, J Am Geriat Soc 2002 (sample size 115)
^20^, Liu, Clin Rehab 2017 (sample size 79)
^21^ and Serra-Prat, Age Aging 2017 (sample size 172)
^2^. The average study size of the 31 studies included in our meta-analysis of frailty interventions
^7^ was exactly 100.

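### A return visit to the practice is the only stated route to three-month SHARE-FI and CFS, so participants who cannot attend because they declined are likely to lack both

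*Protocol article*

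**What the plan says.** The section General considerations fixes the place of measurement: "All measures will be collected in the GP practice setting". The primary outcome is "Frailty status measured by SHARE-FI at three months after the start of intervention", and CFS at the same time is a secondary outcome. Study methods, assessments and procedures gives one route to both: "All participants will be invited to return at three months for a clinical assessment and measurement of health indicators and frailty status". The GP makes the assessment. The article states no home, telephone or carer route for either scale.

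The same section describes a second contact, in one arm only: "Intervention participants will be called after one month and after three months by the GP". Adherence is asked at both calls. Ease and perceived health are asked at three months.

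Other provisions that bear on the point:

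- **Drop-out:** "Enrolment of 210 participants assumes a 15% drop out rate" (Determination of sample size subjects).
- **Analysis set:** the main analysis includes everyone randomised (Analysis sets).
- **Missing data:** chained-equations imputation where appropriate (Procedure for accounting for missing, unused and spurious data).
- **Withdrawal:** mandatory when a participant becomes ineligible during the study (Discontinuation/withdrawal). The exclusion criteria include residential care and CFS above 5.
- **Long-term care admission:** a secondary outcome.

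**The concern.** Participants are 65 or older with CFS 4 or 5 at entry, and the protocol itself treats hospitalisation and long-term care admission as events to be counted. People who have such an event, or simply become too frail to travel, are among those least able to return and most likely to have worsened. If the visit is the only route, attendance can depend on the outcome being measured.

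Imputation does not remove this by itself. A standard chained-equations model predicts missing values from what was observed. Baseline SHARE-FI and age say little about decline after baseline. The drop-out allowance protects the number analysed, not the estimate against selective loss.

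The three-month call adds an imbalance. Only the intervention arm is contacted by telephone around the time of the outcome visit, so attendance could differ by arm for reasons built into the procedures.

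Some of the loss looks avoidable. The Rationale says that overall function, weighed by clinical judgement, "can be assessed by the Clinical Frailty Scale (CFS"). The rater is the participant's own GP, who already collects trial data by telephone.

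**Working it through.** **1. The plan's own sample size.** Inputs from Determination of sample size subjects: 15% v 3% improved to non-frail, type I error 0.05 (taken as two-sided), power 80%, 1:1 allocation. Pooled-variance formula without continuity correction, with mean rate 0.09:

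n per arm = [1.960 × √(2 × 0.09 × 0.91) + 0.842 × √(0.15 × 0.85 + 0.03 × 0.97)]² / 0.12² = 88.1, rounded up to 89, or 178 in total.

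The plan states 176, which is 88 per arm (power 79.96%), so the figure reproduces. For drop-out, 176 / 0.85 = 207.1, or 208 with equal arms, and 210 × 0.85 = 178.5. The enrolment of 210 is adequate in number, so the point concerns bias and not size.

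**2. How many people.** 0.15 × 210 = 31.5, about 32 participants. The article does not say what share of these would be lost because of decline.

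**3. Illustration of selective loss.** Assumptions: true rates of 15% v 3% among all randomised, every missing participant a non-improver, complete cases only. If a fraction m of an arm is missing, the observed rate is the true rate / (1 − m). The true difference is 12.0 points, and the true odds ratio is (0.15/0.85) / (0.03/0.97) = 5.71.

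| Missing, intervention / control | Observed rates | Difference (points) | Odds ratio |
|---|---|---|---|
| 15% / 15% | 17.6% v 3.5% | 14.1 | 5.86 |
| 25% / 5% | 20.0% v 3.2% | 16.8 | 7.67 |
| 20% / 10% | 18.8% v 3.3% | 15.4 | 6.69 |
| 10% / 20% | 16.7% v 3.8% | 12.9 | 5.13 |
| 5% / 25% | 15.8% v 4.0% | 11.8 | 4.50 |

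First row: 0.15/0.85 − 0.03/0.85 = 0.1765 − 0.0353 = 0.141.

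**4. No true effect.** With an assumed 9% improving in both arms, equal loss of 15% leaves no difference. Loss of 25% / 5% gives 0.09/0.75 − 0.09/0.95 = 0.1200 − 0.0947, a spurious 2.5 points.

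**5. What the result depends on.** Under equal loss the odds ratio barely moves (5.71 to 5.86) while the risk difference rises by 14.1/12.0 − 1 = 18%. Unequal loss matters more, and it can push either way.

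**6. The withdrawal rule beside the outcomes.** Entry to residential care and CFS above 5 are exclusion criteria, and ineligibility that arises during the study requires withdrawal. Read together, these could remove the participants who worsened most. That sits badly with an analysis set of everyone randomised and with long-term care admission as an outcome. A telephone call alone would not cure it.

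**The case against.** The strongest reply is that the case rests partly on silence. Nothing forbids scoring CFS by telephone or at home. An article condenses a fuller protocol, training documents are mentioned but not shown, and the schedule of events is a figure that was not available. The plan also requires three documented contact attempts before loss to follow-up, and an end-of-study assessment after withdrawal for an adverse event. Hospital and care admissions and adverse events can be known without a visit and could inform the imputation. This tempers the point without removing it. The setting is a stated rule, the return visit is the only stated route to the two scales, and the telephone calls already depart from the rule as written.

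A reader might go further in four ways that the documents do not support:

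- **That every outcome is collected only at the practice.** Ease and perceived health are asked by telephone in the intervention arm, and hospitalisation and long-term care admission are not said to need attendance.
- **That missing data will concentrate in the worst outcomes and flatter the results.** This is plausible, but no rates are given. The drop-out figure may include consent withdrawal and non-compliance.
- **That the effect would be overstated by 18%.** That is a complete-case risk difference under an extreme assumption. The plan imputes, and it reports frailty categories as an odds ratio.
- **That the feasibility study shows frailty-related non-attendance.** Its remark on "reducing anxiety while housebound during the Covid-19 pandemic" concerns people kept at home by the pandemic.

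It is also fair to say that a call cannot recover a full SHARE-FI, because the scale includes handgrip. Nor does the article list which of its items are self-reported.

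**Conclusion.** The point holds for SHARE-FI and CFS, and not for all outcomes. As written, a participant unable to return at three months has no stated way to contribute either scale, and the named imputation method would not by itself correct loss that depends on unobserved decline.

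Size and direction are unknown. The ranges of 11.8 to 16.8 points and of 4.50 to 7.67 for the odds ratio rest on the plan's 15% v 3%, an assumed loss of 5% to 25% per arm made up wholly of non-improvers, and a complete-case analysis. They show sensitivity and do not predict the trial's result. If the intervention-only call raised attendance in that arm, the pattern would be nearer the last table row, where the effect is slightly understated. The sample size is not in error. The change is worth making because it is cheap and protects the interpretation of the primary endpoint.

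**What to change.** 1. Reconcile the practice-only statement in General considerations with the telephone contacts in Study methods.
2. For any participant in either arm who does not attend at three months, have the GP telephone the participant or carer within the visit window. The GP scores CFS, asks whichever SHARE-FI items are self-reported, and records hospitalisation and place of residence.
3. Use the telephone CFS in the CFS analysis, and the other data as auxiliary variables in the imputation. Add a sensitivity analysis limited to practice-measured CFS.
4. Add a missing-not-at-random analysis for SHARE-FI, for example with non-attenders counted as not improved, or delta-adjusted imputation.
5. Reconcile the withdrawal rule and the exclusion criteria with the intention-to-treat set and the long-term care outcome, so that outcome collection continues for participants who become ineligible during the study. This concerns data collection only. Whether the intervention continues is a separate clinical matter.

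Cost: about 32 short calls by the existing GPs at the planned 15% drop-out, and a small mixed-mode element in CFS, which the sensitivity analysis in step 3 would show. The call does not supply handgrip, so SHARE-FI stays incomplete for these participants and step 4 is needed regardless.
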